For years, pharmaceutical care has been a key strategy to improve healthcare safety. Pharmaceutical care is a collaborative care approach which implies all the actors of the medication circuit in order to prevent and correct DRPs that can lead to ADEs. The collaborative pharmaceutical care performed during patients’ hospitalization requires two complementary activities: medication reconciliation and medication review. First, medication reconciliation is a collaborative process requiring the acquisition of the best possible medication history (BPMH) and its comparison against the hospital medication order [5, 10]. Studies have shown that medication reconciliation had a potential clinical impact by decreasing the rate of hospitalized patients with at least one unintended medication discrepancy (UMD) [10, 11]. This activity could be optimized by a clinical pharmacist based in care units [12]. A few studies have demonstrated that medication reconciliation can reduce readmissions [10, 13], whereas 10–24% of UMDs would lead to severe harm or would be life-threatening [11, 14]. Second, medication review is a multidisciplinary analysis of medication order initiated by the clinical pharmacist [10, 15, 16] that consists of optimizing the medication treatment by improving medication adherence, compliance with the recommendations, and decreasing DRPs (e.g. detection of potential inappropriate medications in elderly [PIM], non-treated therapeutic indications, better matching between medication and therapeutic indication, etc.). Medication review is supported by international standardized tools such as STOPP and START criteria [17, 18], Beers Criteria [19], and the Medication Appropriateness Index [20]. Medication reviews have highlighted PIM representing 16–71% of medications prescribed at hospital admission [21–23]. Moreover, PIM can lead to preventable ADEs [24]. Studies have shown that 38–79% of the patients benefiting from a medication review initiated by a pharmacist had at least one medication change made by the physician in the order [22, 25, 26]. Some studies have shown an impact of medication review on readmission induced by DRPs [25, 27].

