### Setting and population

Six French University Hospitals which benefit from a strong expertise in clinical pharmacy and are dispersed across the country have agreed to participate (Table 1). Each center selected a short-term care unit in a medical specialty which welcomes the elderly. Only units in which there was no clinical pharmacist were eligible. The medical heads of all the units selected agreed to participate in the study.

All healthcare participants volunteered to participate in the study. In each center, two pharmacy students or two pharmacy technicians will participate in the control period (Table 1); two senior clinical pharmacists will participate in the interventional period. In each hospital center, the same clinical pharmacists will detect medication errors in both periods. All the participants benefited from a specific centralized training in order to harmonize their practices in each period. This training was performed over three days, the week before the study started. After data collection, controls will be carried out to ensure that pharmaceutical interventions have not been misclassified.

Patients aged at least 65 years, hospitalized in one of the participating care units, and having given their agreement to be called for a 30-day and 90-day follow-up could be enrolled. In each 14-day period, 15 patients will be recruited in each care unit no more than 24 h or 48 h after admission, respectively, in the week or weekend/public holiday. Finally, a total of 630 patients will be enrolled in the study. We will exclude patients with a hospital stay > 21 days, as there is a risk of there being too many medication modifications during the hospital stay.

The study procedures and assessments are outlined in the Standard Protocol Items: Recommendation for Interventional Trials (SPIRIT) checklist (see Additional file 1) and SPIRIT Figure (Fig. 2).

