### Outcomes

The primary outcome will assess the rate of patients having at least one preventable medication error (e.g. omission, wrong dose, wrong route of administration, etc.) on admission medication order (AMO). The primary outcome will be evaluated by clinical pharmacists retrospectively in the control period and prospectively in the interventional period.

Among the secondary outcomes, the potential clinical impact of each error detected will be assessed by a hospital physician and two clinical pharmacists (different from the investigators) by using a decision algorithm [30] adapted from the NCC MERP’s Index [31] and employing the high alert risk medication list of the Institute of Safe Medication Practices [32] and the North Carolina Narrow Therapeutic Index [33]. All of the experts, who are seniors specialized in geriatrics, will blindly perform the analysis, i.e. without knowing the hospital center concerned, after completion of patient recruitment for all the centers. The potential clinical impact will also be evaluated by the rate of patients at high risk of ADEs according to Trivalle’s score [9, 34].

Other secondary outcomes will be: (1) the acceptance rate of pharmaceutical interventions during the interventional period; (2) the readmission and mortality rates 30 and 90 days after discharge; (3) the length of hospital stays; (4) the satisfaction of care providers involved in the collaborative pharmaceutical care (assessed by postal or electronic mail after the end of the 90-day follow-up); and (5) the induced and avoided costs of the strategy. For this last outcome, we will estimate the induced costs by measuring the time spent performing the collaborative pharmaceutical care. We will also assess the avoided costs by estimating the healthcare consumptions dues to medication errors by using the results of a French national study concerning ADE occurrence and cost [1] and/or by using an expert concertation via a DELPHI method.

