**Fig. 3 Fig3:**
[figure not shown]
MEDREV study - flow of the intervention. BPMH, best possible medication history

In the interventional period, a senior clinical pharmacist based in the care unit will perform medication reconciliation by comparing the BPMH to the AMO and notifying the prescriber of any possible discrepancies. He/She will collect all relevant bioclinical data and perform medication review of the AMO by using the STOPP and START tools [18], the French list of potentially inappropriate medications in elderly [36], and the PAPA guide about medication prescription adapted to the elderly, published by the French Society of Geriatric and Gerontology [37]. The clinical pharmacist will have a collaborative meeting with both the prescriber and the nurse in order to notify any possible medication errors and suggest any proposals to optimize the AMO according to the medical history, the clinical status, and the therapeutic adherence etc. (e.g. change of galenic form due to swallowing problem, dose adjustment to renal function, etc.). After the collaborative meeting, the clinical pharmacist will check whether the prescriber has accepted his/her suggestion(s) and modified the AMO. All the pharmaceutical interventions, i.e. the medication errors detected and the pharmaceutical suggestions of order modification, will be collected and characterized in a standardized form according to the French Society of Clinical Pharmacy [38]. The post-discharge follow-up and the retrospective assessment of the potential harm of each error will be performed as in the control period. At the end of the study, a satisfaction survey will be sent to all the care providers involved in the collaborative pharmaceutical care.

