### Statistical analysis

Descriptive statistics will be reported as counts and percentages for categorical variables, means and standard deviations for continuous variables with normal distribution, and median and quartiles for others. Comparisons of baseline characteristics and of putative risk factors between the two periods will be performed. The primary outcome will assess the rate of patients having at least one preventable medication error through a mixed effect logistic regression model [40]. Let Y_ij_ be the *j*th observation (j = 1…m_i_) in the *i*th cluster (i = 1,2,…,K). The intervention variable is X_*i*_. The logistic mixed effect model is$$ \mathrm{Logit}\left({\mathrm{p}}_{\mathrm{i}\mathrm{j}}\right)={\upbeta}_0+{\upbeta \mathrm{X}}_{\mathrm{i}}+{\mathrm{Z}}_{\mathrm{i}} $$

Where Z_i_ is the random effect for cluster *i*, normally distributed with mean 0 and variance τ^2^, X_i_ is the group indicator. Therefore, the rate of patients having at least one preventable medication will be modeled as:$$ {\mathrm{p}}_{\mathrm{i}\mathrm{j}}=\mathrm{E}\left({\mathrm{Y}}_{\mathrm{i}\mathrm{j}}|{\mathrm{X}}_{\mathrm{i}},{\mathrm{Z}}_{\mathrm{i}}\right) $$

The other effects of putative predictors of the differences in medication adherence between patients from the control and the interventional periods will be evaluated. The secondary outcomes will be evaluated by descriptive and classical statistics: the acceptance rate of pharmaceutical interventions during the interventional period will be estimated (%) only in interventional period; the rate of readmission;, mortality at 30 and 90 days will be estimated and compared using a Chi-square test; the length of stay will be estimated and compared using a non-parametric test; and the descriptive statistics will be used to describe the results or the satisfaction of care providers.

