## Discussion

This trial will investigate the impact of the collaborative pharmaceutical care on preventing and correcting inpatients’ medication errors and costs.

The patient recruitment is a critical parameter to guarantee the study feasibility. The care units participating in the study have been chosen for having more than one eligible patient admission a day. Two-thirds of them are not specialized in the elderly whereas some of them are geriatric specialized units. All are medical units with a large number of beds (more than 15) and a mean length of stay of 2–5 days. In order to be maximally efficient, the intervention will need to start as soon as possible after patient admission. The patient interview during the medication reconciliation process will take around 15 min.

In order to standardize the collaborative pharmaceutical care, the scientific committee has created a specific training program for the students and technicians involved in the control period and for the senior clinical pharmacists involved in the interventional period. This program was elaborated by expert clinical pharmacists who are members of the French Society of Clinical Pharmacy. To ensure the performance of the intervention, they have written quality forms (i.e. checklist process and worksheets). To harmonize the data collection, phone interviews will be centrally performed by two officers.

The next step of this phase III study, if the results lead to effectiveness of the collaborative pharmaceutical care, is to assess the implementation and to determine whether others can reliably replicate the intervention and results in uncontrolled settings over the long term.

This study has the support of the French Society of Clinical Pharmacy which is expected to write recommendations and promote the implementation of the collaborative pharmaceutical care in all French health facilities in order to improve medication safety.

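### The planned predictor analysis names medication adherence, which is not a trial outcome, and the stated primary model has no patient-level term to absorb a within-unit change in case mix

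*Protocol article*

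**What the plan says.** All places are in the protocol article.

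- **Statistical analysis, predictor sentence.** Directly after the primary model: "The other effects of putative predictors of the differences in medication adherence between patients from the control and the interventional periods will be evaluated".
- **Statistical analysis, primary model.** The model is printed as logit(p_ij) = β0 + βX_i + Z_i, where X_i is the group indicator and Z_i a normal random effect for the unit. It contains no patient-level variable.
- **Statistical analysis, baseline data.** "Comparisons of baseline characteristics and of putative risk factors between the two periods will be performed". No use of these comparisons in the model is stated.
- **Outcomes.** "The primary outcome will assess the rate of patients having at least one preventable medication error" on the admission medication order. The secondary outcomes are the potential clinical impact of errors, a score for risk of adverse drug events, "the acceptance rate of pharmaceutical interventions during the interventional period; (2) the readmission and mortality rates 30 and 90 days after discharge", length of stay, care-provider satisfaction and costs. The Abstract and the end of the Background describe the same set more briefly.
- **Design and Blinding.** Only the time at which each unit switches is randomised. The study is open, except for the expert panel that rates clinical impact.
- **Setting and population.** In each 14-day period "15 patients will be recruited in each care unit". Students or technicians work in the control period and senior pharmacists in the interventional period. The same pharmacists detect errors in both.
- **Discussion.** The units were "chosen for having more than one eligible patient admission a day".

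**The concern.** There are two linked problems, of different strength.

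The first is firm. An analysis of predictors needs a defined dependent variable, and the one named here is neither defined nor listed as an outcome. Followed literally, the sentence cannot be carried out. Read loosely, it leaves the analyst to decide which outcome was meant.

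The second is a matter of risk. Randomising the switching order of six units does not balance patients within a unit before and after its switch. If the patients enrolled after the switch differ in baseline risk from those enrolled before it, that difference enters the estimated effect. The one sentence that might have brought patient variables into the model names the wrong outcome and lists no variables, so the stated method offers no correction.

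**Working it through.** **1. Is adherence an outcome anywhere?** Outside the predictor sentence it appears in two places. The Background gives it as one aim of medication review: "optimizing the medication treatment by improving medication adherence, compliance with the recommendations, and decreasing DRPs". The Intervention section gives it as something the pharmacist weighs when making proposals: "according to the medical history, the clinical status, and the therapeutic adherence etc". Neither supplies a measure, a time point or a comparison. It is absent from the outcomes in the Abstract, the Background and the Outcomes section. The mismatch lies within the article.

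**2. The plan's own figure.** The Sample size calculation section gives difference 0.30, variance 0.20, intra-class correlation 0.05, six units, seven periods, 15 patients per cell and power 99%. Two-sided alpha of 0.05 is my assumption. Taking 0.20 as the total variance:

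- N = 6 × 7 × 15 = 630, as stated.
- τ² = 0.05 × 0.20 = 0.01; σ² = (0.20 − 0.01)/15 = 0.01267.
- Hussey-Hughes variance with period effects: Var = Iσ²(σ² + Tτ²) / [(IU − W)σ² + (U² + ITU − TW − IV)τ²], with I = 6, T = 7, U = 21, W = V = 91.
- IU − W = 126 − 91 = 35; U² + ITU − TW − IV = 441 + 882 − 637 − 546 = 140.
- Var = 6 × 0.01267 × 0.08267 / (35 × 0.01267 + 140 × 0.01) = 0.00628/1.843 = 0.00341, so SE = 0.0584.
- Power = Φ(0.30/0.0584 − 1.96) = Φ(3.18) = 99.9%.

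The stated power is reproduced and is not in dispute. Without period effects, as the printed analysis model has none, the SE is 0.0389.

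**3. What the unit effect does and does not absorb.** Suppose a binary risk factor carries error risk r1 when present and r0 when absent, and the intervention does nothing. If its prevalence within a unit falls from q to q − s between conditions, the apparent risk reduction is s × (r1 − r0). Z_i is the same before and after the switch, so it removes stable differences between units but leaves this term.

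**4. Size, under assumptions.** The article gives no risk-factor data. I assume a control risk of 46% (the rate cited for sample size), 50% prevalence in control and no true effect. Spurious risk reduction in percentage points, with the spurious odds ratio in brackets:

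| Risk-factor odds ratio | s = 5 points | s = 10 points | s = 20 points |
|---|---|---|---|
| 1.5 | 0.5 (0.98) | 1.0 (0.96) | 2.0 (0.92) |
| 2 | 0.9 (0.97) | 1.7 (0.93) | 3.4 (0.87) |
| 3 | 1.3 (0.95) | 2.7 (0.90) | 5.3 (0.805) |

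One worked case: risks of 57% and 35% average to 46%, with odds ratio (0.57/0.43)/(0.35/0.65) = 2.46. A 10-point shift gives 0.22 × 0.10 = 0.022 and a 20-point shift gives 0.044. Against SE 0.0584 these are 0.38 and 0.75 standard errors; against 0.0389 they are 0.57 and 1.13. Against the planned difference they are 2.2/30 = 7% and 4.4/30 = 15%. The largest cell in the table is 5.3/30 = 18%. A shift in the other direction would hide benefit by a similar amount.

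**5. How much room is there to choose patients?** More than one eligible admission a day guarantees only something above 14 in 14 days, against a quota of 15, so at that bound there is almost no choice. On the other side, the Discussion gives more than 15 beds and stays of 2 to 5 days. At assumed full occupancy, 15 beds yield 15 × 14/5 = 42 to 15 × 14/2 = 105 admissions of all ages. The eligible share is not given, so the surplus is unknown.

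**The case against.** The strongest reply is that the adherence wording is a slip in an exploratory sentence and touches neither the primary outcome nor the sample size, and that covariate lists belong in an analysis plan that is not shown. The reference to other effects, placed straight after the model, may have been meant to announce further model terms. This limits the second part: what can be said is that the stated model contains no patient-level term. It does not excuse the first part, because an unseen plan does not explain why the article names an outcome that the trial does not have.

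A reader might also infer more than the article supports:

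- **That staff who know the condition select the patients.** The article does not say who enrols or how patients are chosen among those eligible, and the admission figures leave the room for choice undetermined.
- **That covariates will be chosen from baseline tests.** The article says only that the comparisons will be made. It does not say they will select model terms.
- **That outcome assessors differ between conditions.** Those who collect the control-period data differ, but the pharmacists who detect errors are the same.
- **That the number of medicines should enter the primary model.** It comes from a medication history taken by different staff in each condition. Adjusting for a variable whose measurement depends on condition can itself add bias.

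**Conclusion.** The predictor analysis cannot be run as written. This rests on the text alone. That preventable medication error was meant is an inference for the sponsor to confirm.

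The stated primary model also leaves the effect exposed to any within-unit change in case mix between conditions. That change is a possibility that the open, non-individually-randomised design allows, and the article does not demonstrate it. Under the assumed risk factors its size is 0.5 to 5.3 points. That would not overturn an effect near 30 points, but it would matter if the true effect were much smaller. The point merits correction before analysis. It does not call the design or the power into question.

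**What to change.** 1. In the predictor sentence, replace medication adherence with at least one preventable medication error on the admission order, once the sponsor confirms that this was meant.
2. Before the outcome data are analysed, pre-specify a patient-adjusted primary model with age, which eligibility requires to be known, and weekday versus weekend or holiday admission, if recorded. The enrolment window depends on the latter, but the article does not say it is captured as a variable.
3. Use the count of medicines on the medication history only in a sensitivity analysis.
4. Report the unadjusted estimate alongside. In a logistic model the two odds ratios are not the same quantity, even without imbalance.

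The cost is a change of wording and a little more analysis work, with no new patients. Adjustment removes only imbalance in the variables included, so it reduces the risk without eliminating it. Whether the model also needs a period term is a separate matter.

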### Design

A multicentric stepped wedge cluster randomized trial is proposed because randomization of patients was not possible in this study due to the high risk of contamination bias. Indeed, once the clinical pharmacist arrives in the care unit, the collaborative pharmaceutical care will lead to change in medical practices for all the patients, including the control group. Stepped wedge randomized trial designs involve sequential roll-out of an intervention to participants over a number of time periods. By the end of the study, all participants will have received the intervention, although the order in which participants receive the intervention is determined at random. The clusters will be hospital units. Each hospital unit will start with a control period and switch to an interventional period. The study design will be composed of seven consecutive 14-day periods (Fig. 1). Every 14-day period, one further hospital unit will switch to the interventional period until all the units are in the interventional period in the final 14-day period. The randomization by the project methodologist will define the point that each hospital unit will switch from the control to the interventional periods (Table 1).

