**Fig. 1 Fig1:**
[figure not shown]
MEDREV study design

**Table 1 Tab1:** Centers, units, participants in the control period, and switch period

Hospital	Unit	Participants in the control period	Intervention starting period
CHU Rouen	Diabetes, endocrinology and metabolic diseases	Pharmacy students	Period 2
CHU Toulouse	Cardiology	Pharmacy students	Period 3
CHU Nice	Geriatric internal medicine	Pharmacy technicians	Period 4
CHU Grenoble	Geriatric acute medicine	Pharmacy students	Period 5
CHU Strasbourg	Internal medicine	Pharmacy technicians	Period 6
CHU Nîmes	Medical emergency	Pharmacy technicians	Period 7

*CHU* University Hospital Center

A randomized cluster trial would be difficult to conduct because the cluster number would be high and half of them would not benefit from the intervention.

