The economic study proposed is in the form of a cost-consequence one, using the decision tree methodology. The decision tree is a decision support tool that uses a tree-like graph or model of decisions and their possible consequences, including chance event outcomes and/or resource costs. Each node of the tree is associated to a probability and each trajectory is associated to a leaf and a cost. A stochastic analysis will be performed. All probabilities will be associated to a beta distribution and 10,000 Monte Carlo simulations will estimate the mean cost and the associated confidence interval of each group (without vs with pharmacist). The robustness of the results will be checked with the sensitivity analysis. This will be done by performing a second estimation including a new set of parameters in the decision tree, in order to consider the uncertainty due to the sample, specifically on event probabilities and individual costs induced. If the results of global cost are unchanged, then the robustness could be deduced. The Tornado diagram will be used to evaluate and sort the most sensitive parameter.

The Department of Biostatistics, Epidemiology, Public Health, and Health Economics of Nîmes Hospital Center will perform the statistical analysis using R.4.0. (R Development Core Team [2017], R Foundation for Statistical Computing, Vienna, Austria; https://www.r-project.org) and TreeAge Pro 2017 (TreeAge Software, Williamstown, MA, USA; https://www.treeage.com).

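### Readmission, mortality and length of stay are compared by tests with no unit or period term, although the stepped wedge schedule ties condition to both unit and calendar time

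*Protocol article*

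**What the plan says.** In the Statistical analysis section, the primary outcome gets a mixed logistic model in which a normally distributed term "is the random effect for cluster". The section then changes approach: "The secondary outcomes will be evaluated by descriptive and classical statistics". Readmission and "mortality at 30 and 90 days will be estimated and compared using a Chi-square test", and "the length of stay will be estimated and compared using a non-parametric test". No stratification, unit effect or period effect is named for these comparisons.

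The Design section states: "The study design will be composed of seven consecutive 14-day periods". One further unit switches at each period. Table 1 ("Centers, units, participants in the control period, and switch period") gives the start of intervention as periods 2 to 7 for, in order, endocrinology, cardiology, geriatric internal medicine, geriatric acute medicine, internal medicine and medical emergency. The Discussion describes the units thus: "All are medical units with a large number of beds (more than 15) and a mean length of stay of 2–5 days".

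**The concern.** In a stepped wedge trial each unit contributes a different number of control and intervention periods, and control periods come first. A test that pools patients by condition therefore mixes three things: the intervention effect, differences between units, and change over time. Randomising the switch order makes the unit-mix error zero on average over all possible orders. It does not remove that error for the one order used, and a chi-square or rank test does not count it in its variance. Randomisation does nothing about calendar time.

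Readmission, mortality and length of stay are the patient outcomes that the trial observes directly. Either a spurious benefit or a spurious harm could be reported with no intervention effect. The tests are written into the article, and the same section allows for clustering in the primary outcome, so this is a stated choice and not a detail left to an analysis plan.

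**Working it through.** **Inputs.** Six units, seven periods and 15 patients per unit and period (Design; Sample size calculation); switch periods 2 to 7 (Table 1); ICC 0.05, stated for the primary outcome only (Sample size calculation); mean stay 2 to 5 days (Discussion). The article gives no significance level, so two-sided 5% is assumed.

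**The plan's own figures.** 6 × 7 × 15 = 630, as stated. A Hussey-Hughes calculation with difference 0.30, variance 0.20 and ICC 0.05 gives power of 99.9%, consistent with the stated 99%. Both concern the design and the primary outcome; no figure is given for the secondary tests.

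**Unit mix.**

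| Unit (switch period) | Control | Intervention | Share difference (intervention − control) |
|---|---|---|---|
| Endocrinology (2) | 15 | 90 | +5/21 |
| Cardiology (3) | 30 | 75 | +3/21 |
| Geriatric internal medicine (4) | 45 | 60 | +1/21 |
| Geriatric acute medicine (5) | 60 | 45 | −1/21 |
| Internal medicine (6) | 75 | 30 | −3/21 |
| Medical emergency (7) | 90 | 15 | −5/21 |
| Total | 315 | 315 | 0 |

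Non-overlap is (5 + 3 + 1)/21 = 43%. Internal medicine and medical emergency supply 165/315 = 52% of control patients and 45/315 = 14% of intervention patients.

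**Calendar time.** Mean period is 56/21 = 2.67 under control and 112/21 = 5.33 under intervention. The gap is 2.67 periods × 14 days, about 37 days. A drift of 1 percentage point per period (an illustration; the article reports no trend) would bias a crude difference by 2.7 points.

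**Chi-square test, no effect and no trend.** In units of the total outcome variance, the crude difference has variance

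ICC × Σd² + (1 − ICC) × 2/315, with Σd² = 70/441 = 0.1587.

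The chi-square test assumes 2/315. The ratio reduces to 1 + 24 × ICC, since 0.1587 × 315/2 = 25. True type I error is 2 × [1 − Φ(1.96/√ratio)].

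| ICC | Variance ratio | Type I error |
|---|---|---|
| 0.005 | 1.12 | 6.4% |
| 0.01 | 1.24 | 7.8% |
| 0.02 | 1.48 | 10.7% |
| 0.05 | 2.20 | 18.6% |
| 0.10 | 3.40 | 28.8% |

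Simulation of the test (20,000 runs per setting) gave 17.5% to 18.9% at ICC 0.05 for event rates of 5% to 30%.

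**Length of stay.** Assume unit means of 2.0, 2.6, 3.2, 3.8, 4.4 and 5.0 days and no effect. If means rise in switch order, the crude difference is (5×2.0 + 3×2.6 + 3.2 − 3.8 − 3×4.4 − 5×5.0)/21 = −21/21 = −1.0 day, the worst case. Over all 720 orders the mean absolute difference is 0.37 day. Rejection by an unstratified Mann-Whitney test at 5%, over random orders:

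| Unit means | Distribution assumed | Rejection |
|---|---|---|
| 2–5 days | lognormal, CV 0.6 / 0.8 / 1.0 | 54% / 48% / 37% |
| 2–5 days | gamma, shape 2 | 42% |
| 3–4 days | gamma, shape 2 | 11% |

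In the gamma runs, a rank test stratified by unit rejected in 5.8% (2–5 days) and 5.2% (3–4 days), which identifies unit mix as the cause.

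**Precision after adjustment.** With unit and period in the model, the variance of the effect estimate is 2.3 times (ICC 0.01) to 2.7 times (ICC 0.05) the 2/315 that the crude test assumes. Standard errors are about 1.5 to 1.6 times as large.

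**The case against.** Most of the case on the other side concerns scope and size, and much of it stands.

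- *The ICC is borrowed.* The article states 0.05 for medication errors, as a conservative guess at an unknown. A reader might take 18.6% as the plan's own error rate for mortality or readmission; the documents support only a range. Even at ICC 0.005 the test exceeds its nominal level, though slightly.
- *The length-of-stay figures rest on assumptions.* The Discussion gives only a range of mean stay. Spreading six unit means evenly over it, and the distributional shape, are assumed. The 1.0 day is the worst order.
- *The test is not named.* An unstratified rank test is the natural reading of a non-parametric test listed among classical statistics, but it is an inference.
- *The mixes overlap.* One might say that the crude comparison is mainly one set of specialties against another. That goes too far: 57% of the unit distribution is shared, and the two geriatric units (45/60 and 60/45) are near balance and form a third of each condition.
- *Costs.* A reader might infer that the economic results inherit the same bias. The economic plan says "All probabilities will be associated to a beta distribution and 10,000 Monte Carlo simulations will estimate the mean cost", but not where the probabilities come from. The Outcomes section bases avoided costs on a national study and/or expert consultation, and no significance test on cost is planned.
- *Other secondary outcomes.* Expert-rated harm and the adverse drug event risk score are assigned neither test; acceptance and satisfaction are descriptive.

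None of this supplies the missing unit and period terms.

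**Conclusion.** The point holds for readmission, mortality and length of stay. As written, these comparisons are confounded with unit and calendar time, and their nominal 5% level is not kept. For the chi-square test the true level is 6.4% to 28.8% over ICC 0.005 to 0.10, with no time trend assumed; a trend would add bias. For length of stay, read as an unstratified rank test, it is about 11% if unit means span 3 to 4 days and 37% to 54% if they fill 2 to 5 days evenly.

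It would be wrong to infer that the main conclusion is at risk from this: the primary outcome has its own model with a unit effect, and the trial was not sized on these secondary outcomes. The point should be fixed, but it does not undermine the trial.

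**What to change.** Replace the chi-square and non-parametric tests for these outcomes with models that contain a unit effect and fixed period effects:

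- Readmission and mortality at 30 and 90 days: logistic model with a random unit intercept, or unit as a fixed effect where events are rare.
- Length of stay: a mixed model on log days, or a time-to-discharge model, with the same unit and period terms.
- All of them: small-sample inference suited to six clusters, named in advance.

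The printed primary model cannot be copied unchanged, because it has no period term. Stratifying by unit alone would remove the unit-mix error but leave calendar time. Crude rates by condition can still be reported descriptively.

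State where the decision tree's event probabilities come from. If any come from the trial's own counts, take them from the adjusted models.

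The cost is wording and code. Unit and period are known for every patient, so no new data are needed. Intervals will be wider, as the working shows.
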